### Net survival

The analysis will include data on all nets recorded at each time interval. The number of nets in the sample, the proportion of the indicator and 95% confidence interval will be reported. The following indicators will be used and disaggregated by survey time (for example, 0 weeks, 6, 12, 18, 24, 30 or 36 months):Survivorship:Numerator: total number of nets in ‘good’ condition (pHI 0 to 64) plus ‘acceptable’ condition (pHI 65 to 642) hung over a bed × 100Denominator: total number of each net type distributed to surveyed households, excluding a portion (those that may be still in use by others) of the number lost by attrition

Attrition rate-1 for nets that have been destroyed or disposed of:Numerator: total number of each net product documented as lost due to wear and tear(‘torn’, pHI > 642) in surveyed households × 100Denominator: total number of each LLIN type distributed to surveyed households, excluding the number lost by attrition

Attrition rate-2 for nets not available for sleeping under:Numerator: total number of each net product reported as lost for reasons other than ‘torn’ (given away, stolen, sold or used in another location) in surveyed households × 100Denominator: total number of each net product distributed to surveyed householdsAttrition rate-3 for nets used for other purposes:Numerator: total number of each net product reported as being used for another purpose in surveyed households × 100Denominator: total number of each net product distributed to surveyed householdsFor each net product, the survivorship rate plus attrition rate-1, attrition rate-2 and attrition rate-3 will add up to 100%.Kaplan-Meier survival analysis will be used to assess survivorship of nets with the log rank test being used to ascertain whether there are statistically significant differences between the two types of netting.

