### Net survivorship (Sanako, village B)

To measure survivorship, all nets distributed to study subjects will be recorded. At each time point study nets will be visited and the physical presence of the net recorded. Those hanging over a bed will be considered as being in use. If the net is still present in the household, the investigator will record whether the net is being used for its intended purpose. Nets that have never been used will be recorded but excluded from the main analysis. If the net is no longer in the house, the investigator will determine how it was lost. This will be categorised as follows: loss by giving away the net to others to use either voluntarily (given to friends and relatives or sold) or involuntarily (stolen), and loss due to destruction, discarding or using it for alternative purposes because it is perceived as ‘useless’ [14]. These data will allow an estimation of the ‘hanging rate’ of bednets and allow us to better understand the reasons for net attrition.

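### Net loss is classified differently in the field section and the analysis section, and the wear-out rate carries a hole-index condition on nets that are gone, so wear-out attrition is not determinable as defined

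*Protocol article*

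**What the plan says.** The field section on net survivorship (village B) applies at two moments. For a net still in the household, "the investigator will record whether the net is being used for its intended purpose". For a missing net, "If the net is no longer in the house, the investigator will determine how it was lost", and the cause goes into one of two groups. The first is "loss by giving away the net to others to use either voluntarily" or involuntarily, which covers gifts, sales and theft. The second is "loss due to destruction, discarding or using it for alternative purposes because it is perceived as" useless.

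The data analytical plan, under Net survival, uses three rates instead:

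- Rate-1, titled for nets destroyed or disposed of, counts the "total number of each net product documented as lost due to wear and tear", followed by a bracket reading torn, pHI > 642. Its denominator is the "total number of each LLIN type distributed to surveyed households, excluding the number lost by attrition".
- Rate-2 counts the "total number of each net product reported as lost for reasons other than" torn, with a bracketed list: given away, stolen, sold or used in another location. Its denominator is all nets distributed.
- Rate-3 counts the "total number of each net product reported as being used for another purpose in surveyed households", also over all nets distributed.

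Survivorship counts good or acceptable nets hung over a bed. The section states that survivorship and the three rates total 100%.

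**The concern.** Wear-out is the kind of attrition that bears on durability, and the field section says the data should help explain why nets are lost. Two features of the definitions work against that.

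First, a net reused because it is worn out belongs to the wear-out group in the field section and to rate-3 in the analysis, where it sits alongside nets reused while still serviceable. Second, rate-1 is about nets that have been destroyed or disposed of, yet it carries a condition on the hole index. Under Fabric integrity, the index comes from counting holes on the net, and the corresponding analysis is limited to nets found and assessed. A discarded net has no reading at the survey that records its loss. The protocol does not say whether the last earlier reading applies or the household's account is enough.

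Two analysts with the same forms could therefore report materially different wear-out attrition, and neither would necessarily reach the stated total.

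**Working it through.** **1. The two schemes side by side.**

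| Fate of net | Field section | Analysis section |
|---|---|---|
| Given away, sold, stolen | First group | Rate-2 |
| Destroyed or discarded as useless, earlier pHI > 642 | Second group | Rate-1, if an earlier reading counts |
| Destroyed or discarded as useless, no reading > 642 | Second group | Rate-1 by its title, but outside the bracketed condition; not in rate-2's list |
| Reused because useless | Second group | Rate-3 |
| Reused while serviceable | No loss group stated | Rate-3 |
| Torn, still in the house | Not a loss | Not survivorship; rate-1 only if the bracket is read as a condition class |
| Good or acceptable, in storage | Not a loss | None |

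**2. The plan's own figure: the total of 100%.** Let N be nets distributed, L nets lost (discarded, reused or passed on), p the portion excluded from the survivorship denominator, S nets counted as surviving, and A1 to A3 the attrition numerators. As written:

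total = S/(N − p) + A1/(N − L) + A2/N + A3/N

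N = 374 is the LLIN count in the sample size section on net survival. The same section's planning allowance for fabric integrity, 10% loss per year, is borrowed for illustration: 1 − 0.9³ = 0.271, or about 101 of 374 nets. The split below is assumed: 213 good or acceptable and hung, 20 stored, 40 torn but present, 40 discarded as worn out, 10 reused, 51 given away, sold or stolen (sum 374). Then L = 40 + 10 + 51 = 101 and N − L = 273.

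- Rate-1 as discarded nets only (or torn-but-present nets only), p = 0: 213/374 + 40/273 + 51/374 + 10/374 = 57.0 + 14.7 + 13.6 + 2.7 = 87.9% (unrounded sum).
- The same with p = 51: 213/323 replaces 213/374, giving 96.9%.
- Rate-1 as both, p = 0: 80/273 replaces 40/273, giving 102.6%; with p = 51, 111.6%.
- Every term over 374: 314/374 = 84.0% with one of the two groups in rate-1, and 354/374 = 94.7% with both. The last 20/374 = 5.3% is the stored nets.

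The 100% is not reproduced under any of these readings.

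**3. Direction of error in rate-1.** Let W be true wear-out losses, a the share of W reused, and u the share of the remainder without a usable pHI.

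true = W/N; rate-1 as written = W(1 − a)(1 − u)/(N − L)

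The written denominator multiplies the rate by 374/273 = 1.37 (1.43 if 30% are lost). Rate-1 is too low only if the share leaving the numerator, 1 − (1 − a)(1 − u), exceeds L/N, about 27% to 30%. Below that it is too high.

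Take W as half of losses (assumed): 50.5/374 = 13.5%.

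| a | u | Rate-1 over 374 | Rate-1 as written (over 273) |
|---|---|---|---|
| 0 | 0 | 13.5% | 18.5% |
| 0.2 | 0 | 10.8% | 14.8% |
| 0.2 | 0.5 | 5.4% | 7.4% |
| 0.4 | 0.5 | 4.1% | 5.5% |
| any | 1 | 0% | 0% |

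If 40 torn nets still present are also counted, the third row becomes (50.5 × 0.8 × 0.5 + 40)/273 = 60.2/273 = 22.1%. With wear-out at 30% or 70% of losses, the true value is 8.1% or 18.9%; without torn-but-present nets, the written rate runs from 0% to 11.1% or from 0% to 25.9%.

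**The case against.** A reader might infer that wear-out attrition is simply understated, because both the reuse rule and the pHI condition take nets out of rate-1. The documents do not support that. If one third of worn-out nets are reused and the rest counted on report, the numerator over all nets is 50.5 × 2/3 / 374 = 9.0%, but over the written denominator it is 33.7/273 = 12.3%, close to the true 13.5%. With fewer reused, the written rate is too high.

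A reader might also infer that the field record cannot separate reused from discarded nets. That is unproven. The loss form is not shown, the field section names the individual causes within each group, and the questionnaire described under Study procedures lists given away and discarded separately. Finer items may exist. They would not settle the matter, because the two sections would still assign a worn-out, reused net differently.

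The bracket on rate-1 can be read as a label for condition class rather than a measurement requirement. All available village B nets are surveyed every six months, so most lost nets would have an earlier reading. Both points are fair, and they make the 0% result an extreme. The protocol nevertheless adopts neither rule, and an earlier reading could be six months old.

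Finally, the specified comparison between net types is Kaplan-Meier with a log-rank test on survivorship. A worn-out net is not surviving whether it falls in rate-1 or rate-3, and no test on rate-1 is specified. That stands, so a claim that the arm comparison of survivorship is diluted would go too far.

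**Conclusion.** The inconsistency is in the text. A net reused because useless is a wear-out loss in one section and falls in rate-3 in the other, and rate-1 is conditioned on a measurement that cannot be made on an absent net. Wear-out attrition is therefore not determinable as defined and may err in either direction, and the four rates need not total 100%.

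The size is illustrative. Against an assumed true 13.5%, the readings tried give 0% to 22.1%, and the total runs from 87.9% to 111.6%. These figures rest on a borrowed 10% annual loss (a sample size allowance, not an estimate by cause) and on assumed shares of cause, reuse and missing readings. The conflict between the definitions does not depend on them.

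The consequence is confined to the descriptive attrition rates of a tertiary endpoint. It is worth correcting because cause of loss not captured at the visit cannot be reliably recovered later.

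**What to change.** Use one set of loss categories in the field section and the analysis: destroyed, discarded as unusable, reused because unusable, reused while serviceable, given away, sold, stolen, used elsewhere. Then:

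- Define rate-1 by the reported reason for loss (destroyed, discarded or reused because unusable), with no pHI condition. Use the last pHI before loss only as a sensitivity check.
- Limit rate-3 to nets reused while serviceable.
- Give torn nets still present (pHI ≥ 643) and stored nets their own categories.
- Put every category over nets distributed. In the illustration above this gives (213 + 20 + 40 + 40 + 10 + 51)/374 = 100%. The existing exclusion of never-used nets from the main analysis should apply to numerators and denominator alike.

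The cost is a few more items on the loss form and revised definitions in two sections, with no extra visits. The downside is reliance on household report for nets that are gone, which the sensitivity check partly addresses.

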### Study procedures and evaluations

The study villages will be enumerated following normal demographic surveillance procedures and compounds mapped before being randomised to net type. It is intended that LLIN distribution will be completed by July/August 2014. Nets selected for monitoring will be identified by their unique ID, date of donation and located by the village, household number, name of the head of household and user name. Net users who have moved, and taken their nets with them, or withdrawn consent will be recorded on the survey form and on the master list and they will be replaced by another net user from the same compound. If an entire compound refuses to participate another compound will be randomly selected from those remaining.

Surveys will be conducted in village B at 0, 6, 12, 18, 24, 30 and 36 months post-distribution for all endpoints. A standard questionnaire will be used to collect data at each follow-up from the net user, or parent/carer in the case of children. The following information will be recorded: whether the net is hung over the sleeping place at the time of visit, whether it is in storage, being washed, given away or discarded, the method of hanging, whether it can be tucked securely under the mattress all around, and the fabric integrity and the condition of the net. In village B all available nets will be surveyed each time point, in village A only the compounds randomised for sampling at each time point will be surveyed.

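### Survivorship and the three attrition rates use three denominators and leave some nets unplaced, so in general they will not sum to 100% as stated

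*Protocol article*

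**What the plan says.** The Net survival part of the data analytical plan (protocol article) defines four indicators per net type and survey:

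- **Survivorship.** The numerator counts nets in good condition plus those in acceptable "condition (pHI 65 to 642) hung over a bed". The denominator is nets distributed, "excluding a portion (those that may be still in use by others) of the number lost by attrition".
- **Attrition-1.** The numerator is the "total number of each net product documented as lost due to wear and tear", with a torn hole-index threshold (pHI above 642) in brackets. The denominator is the "total number of each LLIN type distributed to surveyed households, excluding the number lost by attrition".
- **Attrition-2.** The numerator is nets lost for reasons other than being torn ("given away, stolen, sold or used in another location) in surveyed households"). The denominator is all nets distributed.
- **Attrition-3.** The numerator is nets put to another purpose. The denominator is again all nets distributed.

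The section then states that, for each product, "the survivorship rate plus attrition rate-1, attrition rate-2 and attrition rate-3 will add up to 100" per cent.

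Two other places bear on this. Under Study procedures and evaluations, the questionnaire notes whether the net is hung and "whether it is in storage, being washed, given away or discarded". Under Net survivorship (Sanako, village B), physical presence is recorded, never-used nets are left out of the main analysis, and a hanging rate is to be estimated.

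**The concern.** Four proportions sum to 100% by construction only if they share a denominator and their numerators place every net exactly once. Neither condition is met.

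- **Denominators.** There are three. Read literally, the attrition-1 denominator removes the very nets counted in its numerator, so that rate is not a proportion of anything. The part of the losses taken out of the survivorship denominator is not quantified.
- **Categories.** A sound net in storage or in the wash is neither surviving nor lost. A torn net still in the house has no clear place: attrition-1 is framed as loss, yet carries a pHI threshold that can be measured only on a net that is still there. The never-used exclusion appears in none of the four denominators.

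At stake is the level and meaning of survivorship, one of the three durability criteria named in the Background. As defined, it partly measures whether a net was hung on the visit day. Distribution is planned for July/August and most rain falls from May to October, so the 6, 18 and 30 month visits fall outside the rains. The documents give no hanging figures by season.

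**Working it through.** **Inputs.** The formulas come from the Net survival analysis section. Village B has 374 LLINs and 167 PPF-LLINs (Sample size rationale, net survival). Loss is planned at 10% of nets per year (Sample size rationale, fabric integrity). The documents give no counts by net state, so those below are assumptions used only to show direction and size. No net is taken as never used.

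**Notation.** D = distributed; S = sound and hung; U = sound, present, not hung; R = torn, still present; T = lost through wear; O = lost for other reasons; P = used for another purpose. D = S + U + R + T + O + P. Let *a* be the part of losses removed from the survivorship denominator, and *A* the losses removed from the attrition-1 denominator.

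Sum as written = S/(D − a) + T/(D − A) + O/D + P/D.

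The stated figure is 100%. It is reproduced when there is no loss and every net is sound and hung (100/100 + 0 + 0 + 0), and otherwise only if the departures happen to cancel.

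**A. Every net fits a category** (D = 100; S = 70, T = 10, O = 15, P = 5; *a* = O = 15):

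| Reading of *A* | Survivorship | Attrition-1 | Attrition-2 | Attrition-3 | Sum |
|---|---|---|---|---|---|
| T + O + P = 30 | 70/85 = 82.4% | 10/70 = 14.3% | 15.0% | 5.0% | 116.6% |
| O + P = 20 | 82.4% | 10/80 = 12.5% | 15.0% | 5.0% | 114.9% |
| O = 15 | 82.4% | 10/85 = 11.8% | 15.0% | 5.0% | 114.1% |

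The unquantified part matters by itself: survivorship is 70/100 = 70.0% with *a* = 0 and 82.4% with *a* = 15.

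**B. Add 10 sound nets not hung and 8 torn nets still present** (S = 52, U = 10, R = 8; T, O, P as in A). Survivorship is 52/85 = 61.2%.

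- Torn nets still present not counted in attrition-1: the sum is 61.2 + 14.3 + 15.0 + 5.0 = 95.5% with *A* = 30, and 92.9% with *A* = 15.
- Torn nets still present counted in attrition-1 (numerator 18): the sum is 61.2 + 18/85 (21.2) + 20.0 = 102.4% with *A* = 15, and 61.2 + 18/62 (29.0) + 20.0 = 110.2% with *A* = 38.

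**C. No loss, 20 of 100 nets not hung.** 80/100 + 0 + 0 + 0 = 80%.

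**D. The protocol's own loss rate.** Three-year loss is 1 − 0.9³ = 27.1%, or 101 of 374 LLINs and 45 of 167 PPF-LLINs. Take P = R = 0, *a* = O and *A* = all lost. For LLINs:

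- All losses torn, all remaining nets hung: 273/374 + 101/273 = 73.0 + 37.0 = 110.0%.
- All losses torn, 55 of 273 not hung (20%): 218/374 + 101/273 = 58.3 + 37.0 = 95.3%.
- All losses for other reasons, all remaining nets hung: 273/273 + 101/374 = 100.0 + 27.0 = 127.0%.

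The same scenarios for PPF-LLINs run from 95.6% to 126.9%.

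**E. Hanging on the day.** With 70 sound nets present and denominator 85, survivorship is 82.4%, 74.1%, 65.9% and 57.6% when 100%, 90%, 80% and 70% of them are hung. No net has been lost or torn between these figures.

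**F. Which repair is needed.** In B, one denominator alone gives 52 + 10 + 15 + 5 = 82%, or 90% if torn nets still present go to attrition-1. One denominator with every net placed gives 62 + 18 + 15 + 5 = 100%. Both repairs are needed.

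**The case against.** The strongest defence has four parts.

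- **Deliberate exclusion.** Taking given-away nets out of the survivorship denominator is a choice with a stated reason (others may still use them), and the section on net survivorship cites a guideline for separating such losses. Deleting the 100% sentence would remove the false statement. The choice is legitimate and the figure can be kept. Deleting the sentence would still leave attrition-1 on a base that excludes its numerator, and unhung sound nets nowhere.
- **Torn nets.** The bracketed pHI threshold can be read as bringing torn nets still present into attrition-1. That stands: they are ambiguous, not clearly omitted. Case B shows the sum misses 100% on either reading.
- **Invented counts.** This also stands. The departures can offset: in B, survivorship as written is 61.2%, against 62.0% under the repaired definition. The examples show that the identity fails, not how far the trial's figures will be off.
- **Low stakes.** Net survival is a tertiary outcome, measured in a different village from the primary bio-efficacy outcome, and the net states are recorded. This limits the severity.

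A reader might also infer more than the documents support:

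- *That the comparison between net types is biased.* Both types are in one village on one survey schedule, and users and surveyors are blinded. A bias would need hanging or loss patterns to differ by net type. Attrition-2 and -3 already share a base.
- *That the Kaplan-Meier analysis is broken because a stored net fails and later revives.* The article does not define the event, and physical presence is recorded separately. If hanging were used as the event, its reversibility would be a problem, but that is not stated.
- *That replacing movers deletes losses.* The rule that "they will be replaced by another net user from the same compound" comes with recording movers on the survey form and master list. All distributed nets are recorded, and the reason for each missing net is sought.

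**Conclusion.** The stated identity is wrong as a general rule. It holds when nothing is lost and every net is sound and hung, or by chance cancellation. Shrinking the denominators pushes the sum above 100%, and leaving nets out of the numerators pulls it below. With assumed counts it ranges from 80% (no loss, one net in five not hung) to 127.0% (planned loss rate, all losses for other reasons). These figures rest on the assumed net states, on taking the excluded part of losses as all losses for other reasons, and on the stated readings of losses by attrition.

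The survivorship level falls in proportion to the share of sound nets not hung on the visit day. This is a problem of level and interpretation; no bias between arms is shown, and neither a failed Kaplan-Meier analysis nor lost records of movers follows from the text. Severity: should-fix, for a tertiary outcome.

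**What to change.** Rewrite the Net survival definitions as follows.

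1. **One denominator for all four rates:** nets of that type distributed, less never-used nets, as the Net survivorship section requires. Report the number never used separately.
2. **Exactly one category per net at each survey:**
   - surviving: present with pHI 642 or below, whether or not hung;
   - attrition-1: discarded or destroyed through wear, plus present with pHI 643 or above;
   - attrition-2: given away, stolen, sold or used elsewhere;
   - attrition-3: used for another purpose.
3. **Hanging rate:** keep it as the separate indicator already planned.
4. **Additional figure:** survivorship excluding nets possibly still in use by others may be given, labelled separately and outside the 100% sum. In example B it would be 62/85 = 72.9%, beside 62.0%.

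The cost is a change of definitions, applied at analysis; no field procedure changes. Presence, hanging, storage, washing, holes and reason for loss are already to be recorded. One check is needed: the Net survivorship section groups alternative use with destruction and discarding, so the dataset must keep these apart for attrition-1 and attrition-3.

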### Tertiary: net survival

Comparisons will be made between functional LLIN survival [14] with both types of nets.

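### Net survivorship is scored as sound and hung at the visit, a state that can reverse, yet Kaplan-Meier and log-rank are applied to it with no separate event stated; sound unhung nets also fall outside the four rates said to total 100%

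*Protocol article*

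**What the plan says.** All references are to the protocol article.

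- **Data collected.** Under Net survivorship (Sanako, village B): "At each time point study nets will be visited and the physical presence of the net recorded". Hanging is recorded as well ("Those hanging over a bed will be considered as being in use"), and so is purpose: "If the net is still present in the household, the investigator will record whether the net is being used for its intended purpose". Reasons for loss are split into giving away, sale or theft on one side, and destruction, discarding or other use of a net seen as useless on the other. The section says the data will yield a hanging rate.
- **Visit states.** Study procedures and evaluations lists what is noted at each survey: "whether the net is hung over the sleeping place at the time of visit, whether it is in storage, being washed, given away or discarded". Village B is surveyed at 0, 6, 12, 18, 24, 30 and 36 months.
- **Definition of survivorship.** In the Data analytical plan, Net survival, the numerator is nets with pHI 0 to 642 that are hung over a bed. The denominator is nets distributed, "excluding a portion (those that may be still in use by others) of the number lost by attrition". Three attrition rates follow: lost as torn, lost for other reasons, and used for another purpose. The section then says that "the survivorship rate plus attrition rate-1, attrition rate-2 and attrition rate-3 will add up to 100" per cent.
- **Arm comparison.** The same section ends: "Kaplan-Meier survival analysis will be used to assess survivorship of nets with the log rank test being used". The endpoint section says "Comparisons will be made between functional LLIN survival [14] with both types of nets", and the sample size section names Kaplan-Meier for that comparison.

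**The concern.** Kaplan-Meier and log-rank take one terminal event per net. The only survivorship definition beside them includes hanging on the day of the visit, which a household can undo and redo. A net in the wash at month 12 and back over the bed at month 18 is not surviving, then surviving, in the tabulated indicator. A standard Kaplan-Meier run on the same state would stop at month 12 with a failure. The table and the curve would then disagree about the same nets.

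Read this way, the curve estimates the chance of never having been found unhung, torn or lost, rather than net life. Failures unrelated to durability would be mixed into both arms, so a real difference between net types would look smaller. A difference between arms in storage or washing habits, if there were one, would look like a difference in durability.

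**Working it through.** **1. Do the four rates total 100%?** The documents give no net counts by state, so assume 100 nets distributed: 60 sound and hung, 10 sound but stored or in the wash, 10 lost as torn, 15 given away, stolen or sold, and 5 used for another purpose.

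- Common denominator of 100: 60 + 10 + 15 + 5 = 90%. The missing 10% is the stored or washed nets.
- Denominators as written, taking the excluded portion for survivorship as all 15 given-away nets and removing all 30 lost nets from the denominator of attrition rate 1: 60/85 + 10/70 + 15/100 + 5/100 = 70.6% + 14.3% + 15% + 5% = 104.9%.
- Denominators as written with no stored or washed nets (70 hung): 70/85 + 10/70 + 20/100 = 116.6%.

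The stated 100% therefore does not reproduce. One cause is the missing category; the other is the differing denominators.

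**2. How far can the table and the curve diverge?** Take nets that are all sound and present for 36 months. Let p be the share unhung at each of the six follow-up visits. The documents do not give p; it is assumed, and independent between visits.

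- Month-36 tabulated survivorship: 1 - p.
- Kaplan-Meier, with the first unhung visit counted as failure: (1 - p)^6.

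| p | Tabulated at month 36 | Kaplan-Meier at month 36 |
|---|---|---|
| 5% | 95% | 0.95^6 = 74% |
| 10% | 90% | 0.90^6 = 53% |

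Independence gives a large gap. At the other extreme, if the same nets were unhung at every visit, Kaplan-Meier would also give 1 - p and the gap would vanish. Under positive correlation the truth lies between: 74% to 95% at p = 5%, and 53% to 90% at p = 10%.

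**3. What happens to the arm comparison?** The sample size section gives 374 LLIN and 167 PPF-LLIN (374 + 167 = 541, matching the stated village B total). Assume true failure of 8% v 5% per six months and the same unhung share q in both arms, independent between visits. The per-visit chance of a counted failure is 1 - (1 - true rate)(1 - q). The hazard ratio is ln[(1 - 0.05)(1 - q)] / ln[(1 - 0.08)(1 - q)]. Power comes from a log-rank simulation that treats nets as independent.

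| q | Control at 36 months, Kaplan-Meier | Control at 36 months, tabulated | Hazard ratio | Power |
|---|---|---|---|---|
| 0 | 60.6% | 60.6% | 0.62 | about 84% |
| 5% | 44.6% | 57.6% | 0.76 | about 55% |
| 10% | 32.2% | 54.6% | 0.83 | about 35% |
| 15% | 22.9% | 51.5% | 0.87 | about 25% |

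The row q = 0 is also the result when the event is restricted to irreversible failure. With equal true failure and equal q, the type I error stayed between 5.1% and 5.5%. Among nets with a first counted failure before month 36 in the 8% arm, 33%, 48% and 57% were later found sound and hung again, for q = 5%, 10% and 15%.

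**The case against.** **The event rule is not written down.** The survivorship numerator is an indicator tabulated by survey time. Carrying it into the Kaplan-Meier analysis is a reading, and the 100% statement points the other way: it makes non-survivors only the three attrition groups, and a stored net is in none of them. This stands. A reader might infer that the plan makes a net in the wash a permanent failure; the document does not say so. What remains is that the section supports two incompatible treatments of the same nets, and the only definition it gives does not suit the method it names.

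**The detail may sit elsewhere.** The endpoint cites a guideline on functional survival, and event coding is often left to a full protocol or analysis plan. Silence alone would be no finding. Here, however, the article does fix a definition, and also a sum that this definition does not satisfy.

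**There is no flat contradiction over presence.** A reader might infer that one section measures presence and another measures hanging. The Net survivorship section records presence, hanging and purpose, and the analysis section derives an indicator from them. The data are sound; the fault is in the scoring.

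**The size is hypothetical and bias between arms is unlikely.** Both are fair. Every p and q is assumed, correlation shrinks the gap, and never-used nets are already excluded from the main analysis. Nets are allocated by compound within the village, look alike, and users and field workers are blinded, so the documents give no reason to expect different hanging habits. A reader might infer inflated false positives; with equal hanging the simulation shows none.

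**Conclusion.** The point holds in a limited form. As defined, survivorship is a reversible state, and the protocol names a time-to-event method for it without stating an event that cannot reverse. Used literally, the definition would make the curve fall below the tabulated proportion, for example 74% against 95% at an assumed 5% unhung, and would dilute an arm difference (hazard ratio 0.62 to 0.76 in the assumed example). Those sizes depend on assumed unhung shares, independence between visits and assumed failure rates, and illustrate direction only.

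The accounting fault does not depend on those rates. Any sound net not hung at a visit has no place in the four rates, so on a common denominator they fall short of 100% by that share, and the differing denominators prevent a dependable total in any case. Net survival is a tertiary endpoint with no stated power target, so this should be corrected but does not threaten the trial's primary conclusion.

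**What to change.** - **Event.** For Kaplan-Meier and log-rank, define failure as the first visit at which the net is torn (pHI 643 or more) or is reported destroyed, discarded or put to another use as useless. This matches the loss categories already in the Net survivorship section.
- **Risk set.** Keep nets that are present but stored, being washed or otherwise not hung at risk.
- **Censoring.** Censor nets given away, sold, stolen or taken away at the last visit at which they were seen, and state the assumption that such loss is unrelated to the net's condition.
- **Hanging.** Report it separately at each survey as the hanging rate the protocol already names.
- **Accounting.** Use one common denominator and add a category for nets present but not hung, so that the rates total 100%.

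The cost is wording only: visit status, reason for loss and hole counts are already collected at each survey. One small downside is that the curve no longer reflects use, which is shown separately.
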